### Customary intervention

Current AT interventions in Canada take place in the community and are provided by registered occupational therapists. According to collaborators at the participating sites, customary interventions are not standardized. For example, family caregivers are not required to be included within the intervention process. Individuals are provided with equipment based on local funding policies and have limited practice time with devices. Follow-up visits are at the discretion of the therapists. Participants in the control group will receive services provided to clients by the health authorities within the study, with no additional intervention from the study.

### Experimental intervention

The experimental intervention will involve a detailed in-home assessment of the older adult’s current AT as well as the negotiation and implementation of a personal AT plan with the care recipient and his or her family caregiver. Conception of the home-based ATPUT intervention as a standardized approach to AT provision was influenced by the work of Roelands, Van Oost, Stevens, Depoorter, & Buysse [34] on the importance of shared decision-making by caregivers and AT users living in the community. It was developed in consultation with clinicians, AT users, and caregivers [29] and was found to be safe, feasible, and relevant to the targeted individuals when tested in a previous study [31]. It consists of 5 key steps described in Table 1.

**Table 1 Tab1:** Steps in the Assistive Technology Provision Updating and Tune-Up Intervention

Step	Objectives	Intervention content
1. Identify and assess the problematic activities with involvement of both the family caregiver and recipient.	Agreement by the family caregiver and recipient on the choice of problematic activities to be targeted and features making them problematic.	Ascertain the difficulties related to the problematic activities and strategies currently used to deal with them.
		Observe how the activity is currently performed and determine the potential for assistance.
		Complete baseline assessment with tests targeting the skills required to perform the activity, if appropriate.
		Determine what can be improved.
Explore possible strategies to address the problematic activities.	Agreement among the family caregiver and recipient on an AT-related strategy to addressed the targeted problematic activities.	Discuss the family caregiver’s and older adult’s current strategies related to ATs.
		Describe the potential AT-related strategies (from simple to more complex);
		Discuss the advantages and disadvantages of strategies related to ATs in general and the targeted activity.
		Discuss their preferences in ways of doing things.
		Explore relevant characteristics of the physical and social environment of the dyad.
		Inform family caregiver and recipient of the skills required to use strategies related to ATs.
		Provide information and/or demonstrate candidate AT-related strategies (photos, scenarios).
		Give feedback in response to ideas/needs expressed by the dyad.
Choose most appropriate ATs solutions.	Agreement on the AT-related strategy to adopt.	Summarize information collected in the previous step.
		Inform family caregiver and recipient about relevant AT-related strategies available to them.
		Arrive at an agreement about the AT-related strategy to use
		Take steps to implement the strategy.
Conduct training.	Implementation of the AT-related strategy by the dyad and competence in utilizing the relevant AT.	Demonstrate the implementation of the AT-related strategy and use of the AT.
		Practice with family caregiver and care recipient.
		Provide feedback.
Evaluate effectiveness of the AT-related strategy.	Determine what additional intervention may be called for and/or motivate family caregiver’ and recipient’s to continue using the AT-related strategy.	Gauge the satisfaction of the family caregiver and recipient with performing the targeted activity and suggest remedies for problems that are noted.

In contrast to current standards of care, the ATPUT intervention will 1) follow a standardized multistep procedure that will be documented during each encounter using a study-specific tool, 2) include additional in-person follow-up visits that are not necessarily part of customary care, 3) involve the AT user and family caregiver collaboratively, and 4) provide AT and AT funding in a timely manner, entailing financial assistance to repair or acquire new AT, and training. In this regard, the frequency and intensity of the experimental intervention is expected to be greater than customary care. Participants will be allowed to pursue complimentary care during the course of the ATPUT intervention. These will be documented in the life changes form.

The intervention will be delivered by registered occupational therapists trained by the research team to use the same standardized approach and materials, based on a treatment manual [31]. To avoid possible contamination, therapists who deliver the intervention to the experimental group will not treat members of the control group.

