### Quantitative sample size

Sample size was calculated for the primary endpoint (22 weeks) for older adults and family caregivers separately and the largest sample size was selected. The sample size for the primary caregiver outcome measure (CATOM) was chosen to detect a 10 % decrease in perceived burden. This is consistent with the caregiver burden change noted in a prior trial using CATOM scores at baseline and after 16 weeks [31]. It indicates a one-level decrease on half of the items for the family caregivers (nearly always → frequently → sometimes → rarely → not at all). The primary older adults’ outcome measure is the SMAF. The sample size was chosen in order to detect an improvement of 9 % following the intervention. This value is intermediate between the minimal detectable difference and the change measured by administering the SMAF in a study examining the impact of a rehabilitation program on individuals with post-cerebral vascular accident [44, 45].

To determine an effect size, Cohen’s *D* was calculated using standard deviations from our prior study [31] and then transformed into Cohen’s *F* [46, 47]. As the effect size was smaller for the SMAF, we used this value to simulate various potential scenarios using G*Power 3.1.0.87. For these simulations we varied several variables including 1) effect size (0.13 to 0.15), 2) correlations among repeated measures (which previous data suggest will be moderate for pre-post intervention and strong between post intervention and long term follow up, e.g. 0.5 to 0.6), and 3) violations of sphericity (due to differences in variances over time, e.g., 0.6 to 0.9). The average of these sample sizes is 102. Based on approximately a 20 % dropout rate for the main trial endpoint (suggested by the prior study in which dropout occurred exclusively due to health related issues, which are common in this population), a sample of 120 dyads will be recruited (40 from each site).

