### Quantitative data analysis of primary and secondary outcome measures

Data will be entered by raters into SPSS statistics data editor (IBM SPSS Statistics) immediately after each evaluation session to decrease the likelihood of missing data. The use of multiple imputation will be explored to deal with any missing data, especially if a participant is unable to be assessed at one of the data collection time-points [48].

To ensure baseline similarity between groups, the experimental and control groups will be compared on socio-demographic and clinical variables with the use of *t*-tests for continuous data and Chi-square for nominal data. Descriptive statistics and histograms will be used to display differences between the groups. A repeated measures analysis of variance will be conducted to analyze dependent variable data, using a Greenhouse-Geisser correction to address issues with sphericity.

Scores for the primary outcome measures (SMAF and CATOM, items 1–14) will be compared between treatment groups over time using an intention-to-treat analysis. Intention-to-treat analysis dictates that all participants are included in the group to which they were allocated for purposes of analysis, whether or not they completed the intervention for that group. The same analysis will be applied to secondary outcome measures, which include the RNLI, CATOM (items 15–18), CBI, self-report FIM and hours of care provided by family caregivers. These secondary outcome analyses will be considered exploratory in view of the increased likelihood of Type I errors resulting from multiple statistical comparisons. Sensitivity analyses will be performed to compare the effect of the interventions on 1) caregiving spouses versus caregiving adult children, and 2) on participants receiving services at the different sites.

To test for changes in family caregiver burden due to the intervention, changes in older adults’ SMAF scores will be correlated with changes in their caregivers’ CATOM scores, using either a Pearson or Spearman correlation depending on the distribution of the data.

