### Quantitative data analysis for intervention information

For both groups, descriptive statistics will be used to characterize therapists’ number, length, and total time of visits; the number, types, and costs of devices; and occupational therapists’ qualifications, years of practice, and years of experience working in this area. Exploratory post-hoc analysis will examine how these intervention elements may have contributed to the various results such as therapist differences, intensity of intervention, delay in receipt of equipment, and types of devices provided.

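### Therapists are nested within arm but the planned repeated-measures ANOVA treats dyads as independent; if outcomes correlate within therapist, the primary tests are anti-conservative

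*Protocol article*

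**What the plan says.** Under Experimental intervention, the Protocol article separates the providers by arm: "To avoid possible contamination, therapists who deliver the intervention to the experimental group will not treat members of the control group". Control dyads receive the usual services of their site from other occupational therapists (Customary intervention).

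The section on analysis of primary and secondary outcomes fixes the method: "A repeated measures analysis of variance will be conducted to analyze dependent variable data, using a Greenhouse-Geisser correction to address issues with sphericity". It applies by intention to treat to the SMAF composite and to CATOM items 1–14. No therapist term is named. Site appears only in a sensitivity analysis.

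Therapists come up in the section on intervention information: "Exploratory post-hoc analysis will examine how these intervention elements may have contributed to the various results such as therapist differences". The sample-size section varies effect size, correlation among repeated measures and sphericity. It uses no ICC, caseload or design effect.

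**The concern.** Had each therapist treated dyads in both arms, differences between therapists would largely cancel in the comparison of arms. With separate therapists they do not cancel: the average quality of the experimental-arm therapists is part of the estimated effect. Separating the therapists is a sound protection against contamination, but the analysis should then reflect it.

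A therapist effect is plausible because the therapist delivers the intervention: assessment, negotiation with both members of the dyad, choice of device, training and follow-up. Greenhouse-Geisser adjusts degrees of freedom for unequal variances and covariances over time within a participant. It leaves untouched any correlation between dyads of the same therapist.

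At stake is the error rate of the two primary tests. So is the claim in the Discussion that the results should carry over to real life, since carrying over to other therapists requires therapist variation to be part of the stated uncertainty.

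**Working it through.** **1. The plan's own figure.** The plan gives an average of 102 dyads before dropout. Alpha, power and number of measurements are not stated, so 102 cannot be firmly reproduced. For the group-by-time interaction at alpha 0.05, averaged over f 0.13–0.15, correlation 0.5–0.6 and epsilon 0.6–0.9, the noncentral F calculation gives 80.9 (4 measurements, 80% power), 95.0 (3, 80%), 105.0 (4, 90%) and 116.2 (2, 80%). The variant with 4 measurements and 90% power lies within 3% of 102. Every variant assumes independent dyads.

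**2. Inputs for the check.**
- From the plan: 102 evaluable dyads with equal allocation, so n = 51 per arm; therapists nested in arm.
- Assumed, because the article does not give them: nominal two-sided 5%; J = 3, 6, 12 or 17 equally loaded experimental-arm therapists; ICC 0.01, 0.05 or 0.10; no clustering in the control arm.

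**3. Formulas.** Caseload m = 51/J. Design effect DE = 1 + (m − 1) × ICC. With one arm clustered, true SE / reported SE = √((1 + DE)/2). Actual Type I error = 2 × (1 − Φ(1.96 / SE ratio)).

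Worst cell: J = 3, m = 17, ICC 0.10. DE = 1 + 16 × 0.10 = 2.60; SE ratio = √1.80 = 1.342; 1.96/1.342 = 1.461; Type I error 14.4%.

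A mild cell: J = 12, m = 4.25, ICC 0.01. DE = 1 + 3.25 × 0.01 = 1.0325; SE ratio = √1.01625 = 1.008; Type I error 5.2%.

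**4. Results, experimental arm only clustered.**

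| Therapists (dyads each) | ICC 0.01 | ICC 0.05 | ICC 0.10 |
|---|---|---|---|
| 3 (17) | 5.9% | 9.8% | 14.4% |
| 6 (8.5) | 5.4% | 7.2% | 9.5% |
| 12 (4.25) | 5.2% | 5.9% | 6.9% |
| 17 (3) | 5.1% | 5.6% | 6.2% |

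Simulated two-sample t-tests (40,000 per cell) agree with these values to within about 0.3 percentage points. At ICC 0.05 the true SE is 9% larger than reported with 6 therapists (√((1 + 1.375)/2) = 1.09) and 18% larger with 3 (√((1 + 1.80)/2) = 1.18).

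**5. Both arms clustered alike.** The SE ratio becomes √DE. At 51 per arm and ICC 0.05, the Type I error is 9.5% with 6 therapists per arm and 14.4% with 3.

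**6. Does this carry over to the planned test?** The Greenhouse-Geisser group-by-time test was simulated under the null: 4 visits, correlation 0.55, a constant therapist effect after baseline only, both arms clustered, 60 per arm, 4,000 runs per cell. At ICC 0.05 it rejected in 16.8% (3 per arm), 10.4% (6) and 7.0% (12). The formula gives 16.0%, 10.4% and 7.4%. With ICC 0 it rejected in 4.6% to 5.3%. So the effect is not an artefact of using a t-test. The one-arm case was not simulated with this test.

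**The case against.** The strongest reply is that nothing in the article shows that clustering exists or matters here. It gives no ICC, therapist count or caseload. ATPUT therapists share training, a manual, fidelity checklists and regular feedback, all of which tend to reduce therapist variation, and outcomes are collected by blinded raters rather than by therapists. Control dyads receive ordinary services at three sites, with no sign that they are concentrated on a few therapists. With 12 or more experimental-arm therapists and a small ICC, the inflation is negligible.

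This stands as far as size is concerned. A reader might infer that the reported standard errors will be too small, or that the error rate will be 10% to 15%. The article does not support either statement: the first needs a positive ICC and more than one dyad per therapist, and the second needs few therapists and an ICC towards the top of the assumed range. The both-arms figures rest on the least evidence.

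It can also be said that the issue is partly handled, because therapist differences will be explored and effects compared across sites. With one ATPUT therapist per site, that comparison would show the heterogeneity. Neither step changes the standard error of the primary test.

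Finally, an unseen analysis plan might add a therapist term. But the article itself names the primary method and assigns therapist differences to exploration, so the point concerns what is stated rather than what is left out.

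**Conclusion.** The point holds in conditional form. The nesting of therapists in arm and the lack of any allowance for it in the stated primary analysis are facts of the article. The direction is fixed: with any positive therapist ICC and shared caseloads, the planned test is anti-conservative. The size is not fixed. With 51 dyads per arm and only the experimental arm clustered, the Type I error ranges from about 5% (12 to 17 therapists, ICC 0.01) to about 14% (3 therapists, ICC 0.10), and is higher if control dyads also cluster.

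A reader might go further and infer that a positive result would merely reflect a few good therapists. The article does not show that. What follows is narrower: the planned analysis could not separate the two explanations. This is a cheap improvement to the plan, not a demonstrated failure of it.

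**What to change.** - Record an identifier for the treating therapist for every dyad in both arms. The planned chart review and therapist survey can supply it.
- Pre-specify, for the SMAF composite and CATOM items 1–14 at 22 weeks, a mixed model with a random therapist effect nested in arm and small-sample degrees of freedom. Use the partially nested form if only the experimental arm clusters. Report the number of therapists, their caseloads and the estimated ICC.
- If therapists are too few to estimate the variance, report the 22-week result under fixed ICCs of 0.01, 0.05 and 0.10 beside the unadjusted ANOVA.
- Limit the statement on transferability to what the therapist-adjusted results support.

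The cost is one data field and some analysis wording. The downsides are wider intervals and, when therapists are few, an imprecise therapist variance. In that case the random-effect model should not be the sole basis for the claim, and the fixed-ICC results carry the argument.

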### Treatment fidelity

We will follow the NIH Behavior Change Consortium’s recommendations [35] for enhancing treatment fidelity. We address considerations of study design (intervention is distinct, based on a conceptual framework), provider training (occupational therapists will be trained on the ATPUT through in-person or video-conferencing, and will be using an intervention manual), treatment delivery (reminder calls before each visit, home environment where the skill is actually performed, treatment planning by the occupational therapists), treatment receipt (checklist of all intervention operations with dates performed), and enactment of treatment (checks if the AT was obtained and if necessary, installed; evaluation of the AT solution during the final visit; adherence form to document the degree of adherence to recommendations). Coordinators will monitor checklists and review interventionist data collection sheets for possible errors and coherence. They will provide individual feedback regularly to occupational therapists and collect their notes, reflections and comments.

### Quantitative measurements

Table 2 highlights the measures to be administered at each time point. Raters will administer all quantitative measures. They will be trained by the study coordinator to ensure standardized administration of the measures. The primary outcome measure for care recipients will be a composite score from two sub-scales of the Functional Autonomy Measurement System (SMAF) [36]. These sub-scales will include self-care and mobility, and exclude the communication and mental functioning sub-scales that are unlikely to be affected by the ATPUT intervention. The SMAF will be administered to care recipients and caregivers together, but all other outcome measures will be administered to them separately. The secondary outcomes will be the self-administered Functional Independence Measure (FIM), a measure of self-assessed independence in daily activities [37, 38], and the Reintegration to Normal Living Index (RNLI), a measure of social participation that address daily activities, roles and relationships [39, 40]. Finally, the SMAF sub-scale relating to instrumental activities of daily living will also be used as a secondary outcome.

**Table 2 Tab2:** Quantitative measures and assessments collected at baseline, week 6, week 22 and week 58

Measures	Tools/Metrics	Baseline	6 weeks	22 weeks	58 weeks
Primary outcomes for AT users	SMAF sub-scales, self-care & mobility	X	X	X	X
Secondary outcomes for AT users	Self-report FIM RNLI EQ-5D SMAF sub-scale, IADL	X	X	X	X
Primary outcomes for family caregivers	CATOM (items 1–14)	X	X	X	X
Secondary outcomes for family caregivers	CATOM (items 15–18) CBI Hours of care	X	X	X	X
Socio-demographic and clinical data for AT users	MoCA^a^ Study-specific questionnaire	X			
Socio-demographic and clinical data for family caregivers	Study-specific questionnaire	X	X	X	X
Treatment fidelity and Intervention information	Adherence Form Life Changes Form Chart review^b^ Therapist survey^b^		X	X	X

*Abbreviations*: *CATOM* Caregiver Assistive Technology Outcome Measurement, *CBI* Caregiver Burden Inventory, *EQ-5D* European Quality of Life, *FIM* Functional Independence Measure, *IADL* Instrumental activity of daily living, *MoCA* Montreal Cognitive Assessment, *RNLI* Reintegration to Normal Living Index, *SMAF* Functional Autonomy Measurement System

^a^MoCA is only re-administered at T1, T2, and T3 if major changes are observed by the raters

^b^Chart reviews and therapist surveys are done at 6 weeks or later

The primary outcome measure for caregivers will be the Caregiver AT Outcome Measure (CATOM) [31, 41]. Construction of the CATOM was based on a conceptual framework of AT outcomes for AT users and their caregivers [30]. The first part (items 1–14) classifies specific activities for which the caregiver provides support, and then measures the frequency of caregiving and the perceived burden associated with the activities (e.g., feeling physically tired after helping with the specified activities). The original CATOM was designed to measure outcomes produced by AT interventions for a single problematic activity, whereas the current study will use a revised version that permits tracking the effects of AT interventions for multiple problematic activities. In the original study, the internal consistency of the activity-specific section of the CATOM was *α* = .73 [31]. The second part of the CATOM measures overall burden and will be used as a secondary outcome measure. The overall burden section is comprised of four items (15–18) measuring the caregiver’s degree of burden associated with all of the assistance provided (e.g., feeling that caregiving duties limits recreational and leisure activities). The internal consistency of this section was *α* = .78 [31]. Other secondary outcomes for caregivers will include hours of weekly care provided, the Caregiver Burden Inventory (CBI) [42], and the European Quality of Life (EQ-5D) visual analog system and descriptive system [43]. The EQ-5D measures the caregivers’ health status; the descriptive system is comprised of 5 items scored from 1 to 3, with higher total scores indicating worse health. The CBI provides a comparative measure of general caregiver burden whereas the CATOM focuses on caregiving as it relates to AT.

Socio-demographic and clinical data will be collected about older adults’ age, sex, level of education, ethnic origin, language, marital status, type of dwelling, diagnoses, duration of functional problems, and amount of formal caregiving received, if applicable. For family caregivers, collected data will include age, sex, level of education, language, the relationship with the older adult and cohabitation (yes/no), employment (yes/no), and duration of assistance.

An adherence form and life changes form will be administered respectively to capture the degree of adherence to occupational therapist recommendations and changing events in the lives of dyad members that could affect outcome measures. Older adults’ and family caregivers’ versions will be administered separately. The life changes form will also capture any adverse events that occur. A chart review of the occupational therapist notes for each dyad will summarize the reasons for referral, the number of visits, the AT provided, and the goals of each session. This review will be conducted after the interventions (customary or experimental) are completed, i.e., six weeks or more following baseline assessment. A therapist survey will also be completed by participating occupational therapists to collect data about their level of education, years of practice, and years of experience working in this area.

